### Plans to promote participant retention and complete follow-up {18b}

Study staff will emphasize the importance of attending all intervention sessions and assessment appointments. We will collect detailed contact information for participants and close contacts. We will reschedule appointments as needed and follow-up with participants who miss sessions and assessments.

### Data management {19}

The PI and UCT PI, CUIMC Project Coordinator, and UCT Project Director will oversee the data management protocol and established Standard Operating Procedures (SOPs) for data collection, quality control, and data extraction and transfer. See the confidentiality section for precautions and quality assurance measures designed to protect the privacy of participants and maintain confidentiality of research data during collection and transfer. To ensure compliance with the monitoring plan, all study staff will be well trained and will receive ongoing supervision in confidentiality and data security procedures, specifically in ethical conduct, confidentiality protection, review of medical records, mandated reporting, data reporting across study sites, and other topics of human participant protection.

Surveys will be administered via password-protected, encrypted tablet computers by individual interview and entered in real time into REDCap projects. Screening, baseline, and follow-up assessments will be conducted in person. Survey data collected on the tablet will be coded with the participants’ ID numbers and will not contain participant names or contact information.

### Confidentiality {27}

Study staff will be trained and will receive ongoing supervision in confidentiality and data security procedures. As part of the consent procedure, participants will be informed of the limits of confidentiality (i.e., reporting of imminent harm to self or others) and mandated reporting requirements (i.e., reporting of child abuse). Interviews, discussions, study assessments, and intervention sessions will be conducted in closed and private rooms on password-protected tablets. Participant information will be stored on password-protected computers or locked cabinets and will not be linked to participant names or locator data. Audio files from intervention sessions will be deidentified and audio-translated into English for quality assurance purposes, and the original files will be deleted upon completion of all analyses. Data will be stored for as long as necessary to complete the study and for adherence to IRB regulations. Biospecimens will be de-identified and destroyed 5 years after study completion. The information gathered in this study will be used only for scientific, educational, or instructional purposes.

### Plans for collection, laboratory evaluation, and storage of biological specimens for genetic or molecular analysis in this trial/future use {33}

Trained personnel will take the blood samples, using only new, sterile equipment, and bandage the site to minimize any potential side effects. Staff will have received prior training in phlebotomy and will review best practices recommended by WHO guidelines on drawing blood. Blood samples will be assigned a unique study ID number and will be stored securely in a locked cabinet at the clinic until they can be transported in a batch to the laboratory for testing. Results will be confidential, following the same procedures as other study data. Viral load results are identifiable only by a study number. Laboratory staff will make results available on a password-enabled, HIPAA-compliant website and will communicate by direct e-mail to the study coordinator.

## Statistical methods

### Statistical methods for primary and secondary outcomes {20a}

To assess intervention effects on the primary outcome (viral suppression), we will compare the proportion of participants achieving HIV viral suppression at 12 month follow-up across study conditions by estimating a risk ratio and obtaining confidence intervals using robust error variances with a modified Poisson model and log link [83]. We will similarly obtain risk ratio estimates to assess intervention effects on the secondary outcomes (i.e., measures of ART adherence and care engagement) using the modified Poisson approach appropriate distribution and link function based on the outcome examined.

To examine the underlying mechanisms of the intervention effects on primary and secondary outcomes at 12 months, we will evaluate the effects of ImpACT + , compared to PST, on hypothesized mediators (e.g., levels of traumatic stress and avoidant coping). Our analytic approach will incorporate the appropriate distribution and link function depending on the distribution of these mediators. We will then examine the effect of both mediators on viral load. If the product of these two paths is greater than zero, this will serve as evidence of mediation [84]. The same approach will be utilized to evaluate the degree to which changes in traumatic stress and avoidant coping mediate intervention effects on secondary outcomes (ART adherence and care engagement).

Finally, qualitative data will be analyzed using a thematic analysis approach [85]. Memos will be written for each transcript to synthesize the emerging themes across the CFIR domains. Themes will be identified via consensus discussion after independent review of transcripts and textually coded using NVivo and/or ATLAS.ti software by multiple coders. Data display matrices will be used to examine commonalities and differences across informants [86]. A diagrammatic visual, overlaid on the CFIR framework [53] will highlight the potential barriers and facilitators to full-scale implementation.

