**Methods:**

This study will be conducted in Khayelitsha, a peri-urban settlement situated near Cape Town, South Africa. Using a hybrid type 1 effectiveness-implementation design, we will randomize 350 WLH initiating ART to the ImpACT + experimental condition or the control condition (three weekly sessions of adapted problem-solving therapy) to examine the effectiveness of ImpACT + on viral suppression, ART adherence, and the degree to which mental health outcomes mediate intervention effects. ImpACT + participants will receive six once-a-week coping intervention sessions and six monthly maintenance sessions over the follow-up period. We will conduct mental health and bio-behavioral assessments at baseline, 4, 8, and 12 months, with care engagement data extracted from medical records. We will explore scalability using the Consolidated Framework for Implementation Research (CFIR).

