### Eligibility criteria {10}

The study will enroll women living with HIV engaging with care at one of the four study clinics. Women will be eligible for enrollment in the trial if they meet the following criteria: (1) Living with HIV and between 2 weeks and 4 months since initiation of first-line ART (as new initiators, restarters or defaulters); (2) history of sexual abuse or assault during childhood, adolescence, or adulthood, using four items based on the WHO CIDI [59] and the Childhood Trauma Questionnaire [60]; (3) endorsement of any PTSD symptoms as assessed by the Breslau PTSD screener [61]; (4) 18 years or older; (5) isiXhosa speaking; and (6) receiving HIV care services at a study clinic. Patients will be excluded and referred to psychiatric services if they meet criteria for high risk of suicide. Suicidal ideation and severity will be assessed using items adapted from the suicidality subscale of the Mini International Neuropsychiatric Interview [62]. Pregnant women will be eligible to enroll. Additional exclusion criteria include patients initiated on second- or third-line ART, the inability to provide informed consent, or inability to communicate in isiXhosa or English.

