### Participant timeline (Table 2) {13}

#### Sample size {14}

Our enrollment target is 350, which will allow detection of intervention effects on viral suppression at 12-month follow-up. Based on data from our preliminary studies [66] and corroborated by national estimates [32], we expect that 57% of women who are newly initiating ART and randomized to the PST condition will be virally suppressed at the 12-month follow-up. With 350 women randomized equally to both conditions, we will have 80% power with a two-tailed alpha level of 0.05 to detect differences between a proportion of 57% in the PST condition and 73% in the ImpACT + condition. This power calculation assumes we will retain 80% of participants over the study period. In the pilot, we were able to successfully retain 80% of all participants (83.3% of newly initiating participants) for the duration of the study [45].

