## Assignment of interventions: allocation

### Sequence generation {16a}

1:1 allocation to either the intervention or control condition will be determined by a random number chart generated using an independent web-based online system (https://www.sealedenvelope.com). Randomization will be stratified by initiation status (naïve initiator, restarter, defaulter), clinic, and pregnancy status (pregnant, not pregnant) to ensure equal distribution of study conditions.

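### The stratification factors (initiation status, clinic, pregnancy) are not carried into the primary modified Poisson model; if they are prognostic, precision is forgone, though the planned power still holds.

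*Protocol article*

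**What the plan says.** Protocol article, Sequence generation {16a}: "Randomization will be stratified by initiation status", and also by clinic and pregnancy status. Study setting {9} gives four clinics, so there are 3 × 4 × 2 = 24 strata. Concealment mechanism {16b} sets blocks of 4 and 6.

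Statistical methods {20a}: the proportions suppressed at 12 months are compared between the arms by "estimating a risk ratio and obtaining confidence intervals using robust error variances with a modified Poisson model and log link". Outcome, effect measure, link and variance estimator are all fixed there. No covariate is named, and the word "unadjusted" does not appear.

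The section on protocol non-adherence and missing data {20c} is the only place where covariates enter an outcome model. They are selected because they predict loss to follow-up, and they are used to see whether the conclusions change. Section {20b} plans no further analyses.

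Eligibility criteria {10} admit women "between 2 weeks and 4 months since initiation of first-line ART". That interval is neither a stratification factor nor a named covariate.

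Sample size {14} states: "With 350 women randomized equally to both conditions, we will have 80% power with a two-tailed alpha level of 0.05". The suppression rates behind that figure are 57% for control and 73% for the intervention, and retention is taken as 80%.

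**The concern.** Stratified randomisation balances the arms on the stratification factors. If those factors predict the outcome, the arm difference varies less from trial to trial than under simple randomisation. An arm-only model does not register this: its standard error still contains the between-stratum variation that the design removed. The interval is then wider than it need be, and the test rejects a true null less often than 5%.

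Initiation status could plausibly be prognostic here. Study setting {9} defines restarters and defaulters by absence from care, which is close to what a suppression outcome measures. The sample size reaches its target at the assumed 80% retention with little reserve, so precision available at almost no cost is worth having. Naming the covariates in advance also closes off a later choice among them.

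**Working it through.** **1. Reproduce the planned figure.** Inputs from Sample size {14}: p1 = 0.57, p2 = 0.73, two-sided alpha 0.05, power 80%, 350 randomised 1:1, 80% retained.

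Per-arm n = [1.96·√(2·0.65·0.35) + 0.8416·√(0.57·0.43 + 0.73·0.27)]² / 0.16² = (1.322 + 0.560)² / 0.0256 ≈ 138.3, so 139 per arm and 278 in total. 278 / 0.8 = 347.5, so 348 against the stated 350.

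With 280 analysed (140 per arm): power = Φ[(0.16 − 1.96·√(0.455/140)) / √(0.4422/140)] = Φ[(0.16 − 0.1117) / 0.0562] = Φ(0.859) ≈ 80.5%.

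On the log risk ratio scale: ln(0.73/0.57) = 0.247; SE = √(0.43/(140·0.57) + 0.27/(140·0.73)) = 0.0896; power = Φ(0.247/0.0896 − 1.96) ≈ 79%.

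The stated 80% is therefore an unadjusted figure, and an arm-only analysis meets it.

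**2. Compare arm-only with adjusted analysis.** The documents do not say how prognostic the factors are, so a range was simulated, with 3,000 trials per scenario under the alternative and 3,000 under the null.

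- From the protocol: 350 women, 24 strata, blocks of 4 and 6, 80% retention, marginal rates 57% and 73%.
- Assumed: initiation mix 50/20/30%, 20% pregnant, equal clinics, dropout at random.
- Assumed log-odds effects, from none to very strong: defaulter against naive 0, −0.5, −1.0, −1.6, −2.2 (restarters half of that); clinic spread ± 0, 0.2, 0.3, 0.5, 0.8; pregnancy, and time on ART across the entry window, each 0, 0.2, 0.4, 0.6, 0.8.
- R² is the resulting share of control-arm outcome variance explained.

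Both models are modified Poisson with an uncorrected robust variance. The adjusted model adds main effects for the three strata and time on ART.

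| Assumed R² | Power, arm-only | Power, adjusted | Interval width, adjusted/arm-only | Null rejection, arm-only | Null rejection, adjusted |
|---|---|---|---|---|---|
| 0 | 80.2% | 80.6% | 0.99 | 4.3% | 4.9% |
| 0.02 | 79.4% | 80.2% | 0.98 | 4.7% | 4.9% |
| 0.06 | 80.2% | 82.1% | 0.965 | 4.5% | 5.2% |
| 0.14 | 80.8% | 85.0% | 0.93 | 3.4% | 5.2% |
| 0.24 | 81.3% | 87.5% | 0.89 | 3.5% | 4.8% |

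Monte Carlo error is about 0.7 points for power and 0.4 points for null rejection.

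**3. Check the mechanism.** Under the alternative, the mean arm-only standard error against the actual spread of the estimates was 0.0901 against 0.0896 at R² 0.06 (ratio 1.01), 0.0901 against 0.0868 at 0.14 (1.04) and 0.0899 against 0.0843 at 0.24 (1.07). The overstatement grows with prognostic strength, as expected.

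**4. A caution on the gains.** The adjusted model's uncorrected standard error ran slightly small: 0.0800 against a spread of 0.0823 at R² 0.24 (ratio 0.97), and 0.0893 against 0.0905 at R² 0 (0.99). Part of the narrowing therefore comes from the uncorrected variance. This is why the fix asks for a small-sample version, which was not itself simulated.

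**The case against.** The strongest reply is that this is a condensed article, that its analysis plan is not shown, and that covariate lists commonly sit there. Section {20a} never calls the model unadjusted, and nothing in it contradicts {16a}. This stands in part: an arm-only model is the natural reading, not an explicit statement. It is still more than silence, because {20a} fixes the rest of the model and {20c} brings covariates in only as a departure from it, to see whether conclusions move.

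A reader might infer that the trial is underpowered. The document does not support that. The 80% is an unadjusted figure and reproduces, and arm-only power stays at about 79–81% in every scenario at the planned rates. A reader might also take the loss of precision as certain or large. It depends on prognostic strength that the document does not give; {16a} gives balance between the conditions, not prognosis, as its reason for stratifying.

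A third inference would be that omitting time on ART or baseline suppression is the same error. It is not. Time on ART is not a stratification factor, so leaving it out forgoes precision but creates no mismatch between design and analysis, and chance imbalance under randomisation is already covered by the interval. For baseline suppression, the abstract says "We will conduct mental health and bio-behavioral assessments at baseline, 4, 8, and 12 months", but section {18a} places blood sampling for viral load at the follow-up assessments and does not mention baseline. A baseline value for every woman cannot be assumed.

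**Conclusion.** The point holds in a limited form. The design stratifies on three factors and the described primary model uses none of them. If the factors are prognostic, the consequence is a conservative test and an interval somewhat wider than necessary. There is no bias, no inflated type I error and no shortfall against the planned power.

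For the strata and time on ART together, adjustment is worth about 1–4% of interval width and 0–2 points of power if they explain up to 6% of outcome variance, and about 7–11% and 4–6 points if they explain 14–24%. The strata alone would give no more than this. Clear conservatism of the arm-only test (about 3.5% instead of 5%) appears only in the stronger scenarios. All these sizes rest on the assumed effects and covariate mix and on dropout at random. The change is worth making because it costs little, not because the trial fails without it.

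**What to change.** State in section {20a} that the primary modified Poisson model contains arm plus main effects for initiation status (three levels), clinic (four) and pregnancy status (two). Enter them as main effects and not as 24 cells, which would average only 280/24 ≈ 12 analysed women each. Specify a small-sample robust variance, a pre-stated fallback if the model is unstable (for example, dropping clinic), and the unadjusted risk ratio as a supportive result.

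Time since ART (re)initiation is known from eligibility and may be added as a prespecified covariate. Add baseline viral suppression only if a baseline value is in fact collected for all participants. If the analysis plan already carries the strata, bring the description in {20a} into line with it.

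The cost is wording and a few degrees of freedom: the strata add 2 + 3 + 1 = 6 parameters, or 7 with a linear term for time on ART. No new data are needed for the strata, which are known at randomisation.

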### Objectives {7}

The primary objective of this trial is to determine the effectiveness of ImpACT + on viral load suppression by reducing avoidant coping and traumatic stress among WLH with sexual trauma in Cape Town, South Africa.

The specific objectives are:To determine the effectiveness of ImpACT + , compared to adapted problem-solving therapy (PST), on clinical outcomes over a 12-month period among WLH with sexual trauma who are initiating ARTTo examine underlying mechanisms of change by evaluating the degree to which improvements in mental health and coping mediate intervention effects on primary (viral suppression) and secondary outcomes (adherence and care engagement)To explore the scalability of ImpACT + , guided by the Consolidated Framework for Implementation Research (CFIR) [53], to better understand facilitators and barriers to full-scale implementation

Our primary hypothesis is that a greater proportion of ImpACT + participants will be virally suppressed (primary outcome), adherent, and engaged in care (secondary outcomes) at 12 months compared to PST participants. Our secondary hypothesis is that over time, ImpACT + participants, as compared to PST participants, will report greater reductions in (1) traumatic stress and (2) avoidant coping, which, in turn, will lead to (causally mediated) improvements in ART adherence, care engagement, and viral load (VL) at 12 months.

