### Outcomes {12}

The primary outcome measure is viral suppression at 12 months, determined by HIV viral copies per milliliter of blood. Viral suppression will be reported as a dichotomous variable with the threshold for viral suppression defined as < 50 copies/mL, as determined by the Abbott Alinity assay (Sensitivity Limit of Detection 20 copies/mL).

The following secondary outcome measures will be assessed at baseline, 4, 8, and 12-month timepoints:ART adherence:◦ Dried blood spots measuring levels of tenofovir-diphosphate (TFV-DP) (at 12 months)◦ Medical record abstraction of pharmacy visits and pharmacy refill data◦ Adapted Adult AIDS Clinical Trials Group self-report measure of adherence [74, 75]HIV care engagement (medical record abstraction):◦ Missed visits (# of monthly visits missed and binary indicator of any missed monthly visit)◦ Visit adherence (proportion of visits kept)◦ Gaps in care (whether > 90 days have elapsed between visits)◦ Visit constancy (# of 90-day intervals with > 1 completed visit).◦ Mental health mediators will be assessed by the following measures (all timepoints):Post-Traumatic Stress (PTSD Checklist-Civilian version for the DSM-5 (PCL-5) [76]Coping [45], adapted from [77–81].

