The second important innovation is that this study will explore whether increased likelihood of viral suppression is mediated by improvements in mental health. Demonstrating that improvement in psychological symptoms mediates the effectiveness of a behavioral intervention to improve adherence will strengthen the case for mental health services to be integrated in primary health care settings, particularly in the context of large mental health treatment gaps in LMICs [91]. In the absence of adequate numbers of trained psychologists and other mental health specialists, the use of culturally appropriate, manualized, and task-shared approaches becomes even more compelling. Given the sensitivity required to broach topics of sexual trauma and the potential for vicarious trauma, ImpACT + is intended for delivery by trained and supervised interventionists. Nurses and social workers are frequently employed in primary healthcare settings and are therefore the most likely candidates for interventionists. These cadres represent a key resource in the South African primary health care system, as well as in many other LMIC.

The third innovation is that we will report on critical implementation outcomes within the context of primary health care. Qualitative data from interventionists, facility managers, local stakeholders, and WLH with lived experience of trauma will inform potential and plans for implementation. Therefore, this trial will systematically evaluate feasibility and acceptability in addition to primary effectiveness. The implementation outcomes of this study will be presented to key stakeholders for consideration for adoption in health system training and capacitation programs. Our goal is to contribute to future policy and practice in the wider health care system.

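### The mediation aim concerns viral suppression, but the secondary hypothesis and the mediation model name viral load, an unlisted outcome for which the stated sign rule runs the wrong way

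*Protocol article*

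**What the plan says.** All references are to the protocol article.

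- **Objectives {7}, specific objective 2** asks how far "improvements in mental health and coping mediate intervention effects on primary (viral suppression) and secondary outcomes (adherence and care engagement").
- **Objectives {7}, secondary hypothesis** expects reductions in traumatic stress and avoidant coping to lead to ("causally mediated) improvements in ART adherence, care engagement, and viral load (VL) at 12 months".
- **Outcomes {12}**: "The primary outcome measure is viral suppression at 12 months, determined by HIV viral copies per milliliter of blood". It adds: "Viral suppression will be reported as a dichotomous variable with the threshold for viral suppression defined as < 50 copies/mL". The assay detection limit is given as 20 copies/mL. Viral load as a quantity is not listed as an outcome of its own.
- **Statistical methods {20a}** gives the purpose of the mediation analysis: "To examine the underlying mechanisms of the intervention effects on primary and secondary outcomes at 12 months". For the path from mediator to outcome it says "We will then examine the effect of both mediators on viral load", and the decision rule is "If the product of these two paths is greater than zero, this will serve as evidence of mediation".
- **Discussion** presents as an innovation that "this study will explore whether increased likelihood of viral suppression is mediated by improvements in mental health".

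**The concern.** Suppression and viral load come from the same blood test but are different endpoints. The primary effect is a risk ratio for being below 50 copies/mL. An indirect effect on viral load is not a component of that risk ratio, so it cannot say how much of the primary effect runs through traumatic stress or coping. The protocol gives no scale, transformation or definition for viral load, and nowhere says that the term stands for suppression.

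The choice of endpoint also sets the sign of the product of paths, and the protocol's rule depends on that sign. At stake is what can be concluded about the primary outcome under one of three specific objectives, which the Discussion also claims as an innovation.

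**Working it through.** **1. The plan's own figure.** Inputs from Sample size {14}: 350 women randomised equally, 80% retained, so 350 × 0.80 / 2 = 140 per arm; 57% v 73% suppressed; two-sided alpha 0.05.

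Power = Φ{[|d|√n − 1.96√(2p̄q̄)] / √(p₁q₁ + p₂q₂)}, with d = 0.16, p̄ = 0.65, p₁q₁ = 0.57 × 0.43 = 0.2451 and p₂q₂ = 0.73 × 0.27 = 0.1971.

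- |d|√140 = 1.893
- 1.96 × √0.455 = 1.322
- √0.4422 = 0.665
- (1.893 − 1.322) / 0.665 = 0.859, and Φ(0.859) = 0.805

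The stated 80% reproduces. It rests on suppression proportions only, so the choice of mediation endpoint does not touch it. The protocol gives no power for mediation.

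**2. Endpoint named at each place.**

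| Place | Endpoint for mediation |
|---|---|
| Specific objective 2 | viral suppression |
| Secondary hypothesis | viral load |
| Statistical methods {20a}, stated purpose | primary outcome, hence suppression |
| Statistical methods {20a}, model | viral load |
| Discussion | viral suppression |

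**3. Sign of the product.** Let a be the effect of ImpACT+ on the mediator and b the effect of the mediator on the outcome. Benefit through lower stress or avoidance means a < 0.

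- Suppression: a higher mediator makes suppression less likely, b < 0, so ab > 0.
- Viral load: a higher mediator raises viral load, b > 0, so ab < 0.

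The rule therefore accepts the hypothesised benefit for suppression and rejects it for viral load.

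**4. How far the two endpoints can disagree.** The protocol gives no mediator or viral-load distribution, so the inputs here are assumptions. In both simulations there are 140 women per arm, the arm effect on the mediator is −0.4 SD, and suppressed women are set at 20 copies/mL. Mediation is declared when both paths have p < 0.05. That is not the protocol's rule; it isolates the endpoint question from the sign question. Suppression is modelled by modified Poisson and viral load by least squares with robust errors.

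*Simulation one* (1,000 trials; unsuppressed log10 viral load with mean 3.5, SD 1):

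| Mediator acts on | log10 viral load | Suppression | Trials that disagree |
|---|---|---|---|
| Suppression (log-odds 0.5 per SD) | 84% | 88% | 5% |
| Level among unsuppressed only (0.6 log10 per SD) | 69% | 4% | 69% |

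In the first row the product was negative for viral load and positive for suppression in every trial, as step 3 predicts. In the second row it was positive for viral load in 0.3% of trials.

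*Simulation two* (2,000 trials per scenario; unsuppressed mean 4, SD 1):

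| Mediator acts on | Suppression | log10 viral load | Raw copies/mL |
|---|---|---|---|
| Suppression (log-odds 0.4 to 0.6 per SD) | 79% to 92% | 74% to 91% | 8% to 17% |
| Level among unsuppressed only (0.5 log10 per SD) | 4% | 60% | 37% |

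**5. Why log10 viral load tracks suppression.** Under the inputs of simulation two, the gap between groups is 4 − log10(20) = 4 − 1.30 = 2.70. With a fraction p unsuppressed, between-group variance is p(1 − p) × 2.70² and within-group variance is p × 1².

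- p = 0.27: 1.44 between, 0.27 within; share between = 1.44 / 1.71 = 84%
- p = 0.43: 1.79 between, 0.43 within; share between = 1.79 / 2.22 = 81%

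So 81% to 84% of the variance in log10 viral load is the suppressed/unsuppressed contrast itself.

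**The case against.** The strongest reply is that viral load is shorthand. The paragraph in Statistical methods {20a} opens with primary and secondary outcomes and ends by extending the same approach to the secondary ones, so the sentence between them fills the primary-outcome slot. The primary objective and the Discussion also use a mixed term, viral load suppression, and the sign rule suits suppression. This reading is plausible and may be what was meant. It does not remove the point: the hypothesis and the model would still name the wrong endpoint, and nothing in the text equates the two.

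A second reply is that viral load, taken literally, is what the secondary hypothesis names. It is measured at follow-up (Plans for assessment {18a}), so finding mediation of it would be a correct result for that hypothesis. That stands, but it leaves objective 2 unanswered for the primary outcome, and the sign rule would still be wrong.

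A third reply is that log scale, censoring at the detection limit and adjustment for arm belong in an analysis plan that is not shown. That also stands; their absence is not criticised here.

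**Conclusion.** The inconsistency is real and on the face of the protocol article. Read literally, the stated mediation model estimates no indirect effect on the primary outcome, and its decision rule would reject beneficial mediation of viral load. Read as shorthand, the endpoint is misnamed in two places.

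A reader might infer more: that the planned test will often give a wrong answer, or that a viral-load slope mainly reflects levels among the 27% to 43% of women expected to be unsuppressed. The documents do not support that.

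- On the log10 scale most of the variance is the suppression contrast. When the mediator acts on suppression, which is the pathway argued in Background and rationale {6a}, the two endpoints nearly agree.
- The large gaps need either a raw copies/mL model, which the protocol does not propose, or a mediator that has no effect on suppression.
- The simulated percentages rest on assumed inputs and a different decision rule, so they are not properties of the planned test.

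Nor does objective 2 fail as a whole: it also covers adherence and care engagement, which the method analyses as named. The primary hypothesis, primary analysis, sample size and data collection are unaffected. The correction should be made, but it is confined to the mechanism aim.

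**What to change.** In Statistical methods {20a}, and in the secondary hypothesis under Objectives {7}, name viral suppression (< 50 copies/mL) at 12 months as the outcome of the mediation analysis. Model it on the same risk-ratio scale as the primary analysis, so that the indirect effect can be read against the primary risk ratio. If viral load is kept, label it an additional exploratory outcome and state that beneficial mediation is expected to give a negative product.

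The cost is wording in two places and a matching line in the analysis plan, with no new data and no change to the 350. The small downside is that information on viral-load level among unsuppressed women leaves the main mediation test.
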